#### 8.4. Baseline Assessments

Prior to randomisation the following information will be collected:

- Patient demographics (gender, age at surgery, body mass index)
- Summary medical history
- Summary medication history (current medication and duration of current medication, changes to current medication in the last 6 months, any history of prior opiate use)
- Quality of Recovery 40
- Pain Visual Analogue Scale (0-10) at rest
- Oxford Knee Score
- Clinical Assessment - American Knee Society Score
- Patient expectations of treatment
- Summary healthcare and social services use as well as informal care in the past 6 months due to knee (GP visits, outpatient visits, allied healthcare contacts, hospital admissions, medications, meals on wheels, and unpaid care)
- Summary employment history (in paid employment, not in employment, time away from work or usual activities)
- EuroQol EQ-5D-5L

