As secondary analyses both pain and QoR-40 measured at 6, 24, 48 and 72 hours will be assessed using longitudinal methods to take account of the multiple-time points and the correlation between them. Multi-level, multivariate linear regression modelling with adjustment for the same factors as the primary analysis will be used. Other continuous variables will be analysed using similar methodology. For binary variables the number and percentage of patients in each category will be reported for each treatment group and overall. Chi-squared tests will be utilised for comparing the treatments, with additional analyses being undertaken using multi-variable logistic regression with adjustment for stratification and other important prognostic factors if sufficient events have been observed.

Reporting of the results will be based on the CONSORT statement.

It is anticipated that all statistical analysis will be undertaken using Stata (StataCorp LP, [www.stata.com](http://www.stata.com)) or other well-validated statistical packages.

Health Economic Analysis: A cost utility analysis will also be performed using quality-adjusted life years (QALYs) as the main health outcome, obtained using the EuroQol EQ5D-5L questionnaire at baseline, 72 hours, 6 weeks, 6 months and 1 year. The perspective of the analysis will be societal and costs will be informed by collecting data on the initial surgery, cost of treatment and analgesic medication, primary/hospital and social care resource use over the first year following surgery, out-of-pocket expenses (e.g. over the counter medications, travel costs to attend consultations, private practitioners, etc.), unpaid care from family members or friends and loss of earnings resulting from knee replacement. Such data will be collected from hospital medical records and using self-completed patient questionnaires at 6 weeks, 6 months and 12 months. Healthcare and social care utilisation will be valued using national databases [33, 34].

The results of the cost utility analysis will be presented using an incremental cost-effectiveness ratio expressed as cost per QALY gained and interpreted as the additional costs/savings associated to the additional QALY benefits of Liposomal bupivacaine compared to Bupivacaine hydrochloride.

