## 6. ANALYSIS

### 6.1 Outcome Definitions

The **co-primary outcome measures** in this trial are the Quality of Recovery 40 score and the cumulative daily pain score both measured at 72 hours post-surgery.

Quality of Recovery (QoR) 40 score – a five dimension validated patient reported peri-operative recovery score that has been widely used across a range of surgeries including knee replacement and assesses overall post-operative recovery [19]. It consists of 40 items each of which is graded on a five-point Likert scale. Total scores are calculated by summing the individual items. QoR-40 scores range from 40 (extremely poor quality of recovery) to 200 (excellent quality of recovery) [18]. The primary time point will be 72 hours post-surgery.

This outcome will also be measured at 6, 24 and 48 hours post-surgery and at 6 weeks, 6 and 12 months post-randomisation.

Cumulative daily pain score – pain at rest will be measured using a visual analogue scale (VAS) ranging from 0 (no pain) to 10 (worst possible pain). Measurements taken as close as possible to 6, 24, 48, and 72 hours post-surgery will be included in the primary outcome assessment. This outcome will also be measured at 6 weeks, 6 and 12 months post-randomisation.

The **secondary outcome measures** in this trial are cumulative opiate use, the Oxford Knee Score, the American Knee Society Score, fitness for discharge, and the co-primary outcome measures at additional time points. The health economics outcomes in this trial include summary medication history, EQ-5D-5L, summary healthcare and social services use, and summary employment history.

Cumulative opiate use – all opioids used on evening of surgery (day 0) and days 1, 2, and 3 will be recorded and a running total of cumulative opioid use calculated. A list of acceptable opioids is provided in the trial protocol.

Fitness for discharge – this will be assessed against pre-defined criteria on evening of surgery (day 0) and days 1, 2, and 3 following surgery as per routine clinical care. Patients will be considered fit for discharge when they meet four criteria: (i) ability to mobilise independently; (ii) pain score less than or equal to 3 on a 10 score VAS scale; (iii) ability to straight leg raise; and (iv) ability to bend knee to 90 degrees. It will also be recorded whether patients were discharged, and if they were not discharged when fit for discharge the reasons for this will be collected.

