## 6.2 Analysis Methods

### Primary outcomes

### Primary analysis

QoR-40 scores at 72 hours post-surgery will be summarised by treatment group using unadjusted means and associated SDs (see Table 10). QoR-40 scores from baseline to 12 months post-randomisation will also be summarised by treatment group using a boxplot.

A mixed effects linear regression model adjusting for type of surgery, baseline QoR-40 scores, age, and gender as fixed effects and recruitment centre as a random effect will be used compare QoR-40 scores at 72 hours post-surgery. The adjusted mean difference between the arms, associated 97.5% confidence interval and associated p-value will be reported (Table 10). The assumption of approximate normality of the residuals will be assessed graphically.

Pain scores from baseline to 12 months post-randomisation will be summarised by treatment group using a boxplot.

A summary statistics approach will be used to calculate the area under the curve (AUC) of cumulative daily pain scores from 6 to 72 hours post-surgery [24]. Specifically, parameters from a repeated measures mixed effects linear regression model will be used to calculate the pain AUC for each treatment group. The model will include repeated measures of the pain scores (level 1) nested within participants (level 2) and adjusted for recruitment centre as a random effect (level 3). Time will be treated as categorical and a treatment by time interaction will be included. The model will be adjusted for type of surgery, baseline pain score, age, gender, and the use of pre-operative opiate pain medication as fixed effects. The AUC for each treatment group and associated SD will be calculated following the formula lay out by Bell et al. [24] and using the lincom command in Stata. Time will be treated linearly and AUCs will be calculated for the median values of continuous covariates and most common value of categorical covariates. These results will be presented as shown in Table 10. Similar methods will be used to calculate the difference between the two groups which will be compared using a t-test. The adjusted difference (97.5% CI) and associated p-value will be presented (Table 10). The assumption of approximate normality of the residuals of the mixed effects model will be assessed graphically.

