|                       | 6 months | X (X)                  | X | X (X)                  | X | X (X,X)                | X       |
|                       | 1 year   | X (X)                  | X | X (X)                  | X | X (X,X)                | X       |
| AKSS - Function       | 6 weeks  | X (X)                  | X | X (X)                  | X | X (X,X)                | X       |
|                       | 6 months | X (X)                  | X | X (X)                  | X | X (X,X)                | X       |
|                       | 1 year   | X (X)                  | X | X (X)                  | X | X (X,X)                | X       |
| Cumulative opiate use |          | X (X)                  | X | X (X)                  | X | X (X,X)                | X       |

Or Median (IQR)

Fitness for discharge is a binary variable. The number and percentage of patients fit for discharge at days 0, 1, 2 and 3 following surgery will be summarised by treatment group (see Table 13). Any instances where someone is fit for discharge at one time point and not at some subsequent one will be summarised. The two treatment groups will be compared using a multi-level logistic regression model with repeated measures (level 1) nested within participants (level 2) and adjusted for recruiting centre as a random effect (level 3). The model will also be adjusted for type of knee replacement, age and gender as fixed effects. Time will be included as a categorical covariate and a treatment-by-time interaction will be included. Adjusted ORs and associated 95% confidence intervals will be reported at each time point (see Table 13). Unadjusted ORs will also be calculated.

Fitness for discharge and actual discharge status will also be summarised by treatment group at each time point (see table 14). Reasons for discrepancies will also be summarised. The average lengths of time from surgery to being determined fit for discharge and from being determined fit for discharge to being discharged will be summarised by treatment group using medians and IQRs.

**Table 13:** Analysis of secondary outcomes (categorical)

|                       |       |  | Intervention |   | Control |   | Difference (95% CI) |         |
|-----------------------|-------|--|--------------|---|---------|---|---------------------|---------|
|                       |       |  | N            | % | N       | % |                     |         |

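### The fitness-for-discharge model omits baseline pain, which the SAP's own pain models include: the analysis is valid but forgoes a little precision

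*Combined protocol and SAP*

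**What the plan says.** SAP 6.1 defines fitness for discharge by four criteria that must all be met. One is pain: "ii) pain score less than or equal to 3 on a 10 score VAS scale". The other three are functional: mobilising independently, straight leg raise and knee flexion to 90 degrees. Fitness is recorded on the evening of surgery and on days 1, 2 and 3.

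SAP 6.2 (Secondary outcomes) analyses it with a multi-level logistic model, with repeated measures "nested within participants (level 2) and adjusted for recruiting centre as a random effect (level 3"), categorical time and a treatment-by-time interaction. On fixed effects it says: "The model will also be adjusted for type of knee replacement, age and gender as fixed effects". On reporting it says: "Adjusted ORs and associated 95% confidence intervals will be reported at each time point", and then: "Unadjusted ORs will also be calculated".

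For pain over the same days, the primary AUC model in SAP 6.2 is "adjusted for type of surgery, baseline pain score, age, gender, and the use of pre-operative opiate pain medication as fixed effects". The secondary repeated-measures pain model uses the same set.

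Protocol 8.4 lists "Pain Visual Analogue Scale (0-10) at rest" among the items collected before randomisation, together with a medication history that covers prior opiate use. For binary outcomes, protocol 11.1 (repeated in SAP 3.7) foresees logistic regression with "adjustment for stratification and other important prognostic factors if sufficient events have been observed".

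**The concern.** The SAP treats baseline pain as prognostic for post-operative pain. Post-operative pain decides one of the four fitness criteria, on the same days. The fitness model nevertheless leaves baseline pain out, without a reason, although the protocol's general rule for binary outcomes points to important prognostic factors.

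What is at stake is efficiency. If baseline pain predicts who becomes fit for discharge, leaving it out makes the day-specific odds ratios less precise than data already in hand would allow. The trial was sized on QoR-40 and pain AUC, so this outcome has no planned margin of power of its own. It is also the secondary outcome closest to the early mobilisation and discharge described in the protocol's background. The co-primary results are not affected.

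**Working it through.** **Plan's own figures.** No sample size or power is stated for fitness for discharge. The co-primary figures reproduce with n per arm = 2(z₀.₉₈₇₅ + z₀.₉₀)² × (SD/difference)².
- QoR-40: 2 × (2.241 + 1.282)² × (15.5/5)² = 238.5, so 239 (plan: 240).
- Pain AUC: 2 × (2.241 + 1.282)² / 0.33² = 227.9, so 228, or 224 if 33% means one third (plan: 225).
- Dropout: 240/0.96 = 250 and 225/0.90 = 250 per arm, as planned.

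None of these depends on the fitness model.

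**Inputs for the check.** From the documents: 500 patients, 1:1, four assessments, a participant random intercept, categorical time and treatment by time. Assumed, because the documents give no values: participant SD 2.0, log odds ratio 0.8 on every day, fitness rising over days 0 to 3, and a latent-scale correlation between baseline pain and fitness of 0.1 to 0.5. Centre, procedure, age and gender were left out for simplicity.

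**Set-up.** Total latent variance = 2.0² + π²/3 = 4 + 3.29 = 7.29, whose square root is 2.70. For correlation r, the covariate coefficient per SD is 2.70r, and the remaining participant SD is √(4 − 7.29r²). At r = 0.4 the coefficient is 1.08 and the remaining SD is √(4 − 1.166) = 1.68. Each setting has 120 simulated trials, fitted with and without the covariate.

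| r | Odds ratio per SD, exp(2.70r) | SE ratio (with/without), days 0, 1, 2, 3 | Effective sample-size gain, 1/ratio² − 1 |
|---|---|---|---|
| 0.1 | 1.31 | 0.998, 0.996, 0.997, 0.998 | 0.4% to 0.8% |
| 0.2 | 1.72 | 0.990, 0.987, 0.989, 0.990 | 2.0% to 2.7% |
| 0.3 | 2.25 | 0.975, 0.972, 0.973, 0.976 | 5.0% to 5.8% |
| 0.4 | 2.94 | 0.957, 0.947, 0.948, 0.961 | 8.3% to 11.5% |
| 0.5 | 3.86 | 0.934, 0.913, 0.913, 0.935 | 14.4% to 20.0% |

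On day 1 at r = 0.4 the SE falls from 0.300 to 0.284. The half-width of the 95% interval for the log odds ratio falls from 1.96 × 0.300 = 0.588 to 1.96 × 0.284 = 0.557.

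**Does omission shift the estimate?** The true log odds ratio is 0.80. Median day-specific estimates at r = 0.1 were 0.742 to 0.907 without the covariate and 0.750 to 0.901 with it. At r = 0.4 they were 0.754 to 0.861 without and 0.739 to 0.840 with. Omission produces no consistent shift towards zero. The simulation error of each figure is roughly 0.36/√120 = 0.03.

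**Second check, a simpler model.** This is ordinary logistic regression on one day, with control fitness of 20% or 50%, odds ratio 1.7 and 3,000 trials per setting. Here adjustment raises the SE (ratio 1.06 to 1.07 at r = 0.4) but moves the log odds ratio further from zero. The gain, measured by the squared ratio of the z statistics, is about 1% at r = 0.1, 3% at 0.2, 5% to 7% at 0.3 and 11% to 14% at 0.4. With no treatment effect and r = 0.4, the type I error was 5.3% to 5.7% without the covariate and 4.6% to 4.8% with it. Both are compatible with 5%.

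**The case against.** The strongest reply is that this is a preference, not a fault. Fitness has no baseline value of its own, so the habit of adjusting each outcome for its own baseline is not broken. Pain is one criterion of four. Both stratification factors are in the model, procedure as a fixed effect and centre as a random effect, and unadjusted odds ratios are reported too. The outcome is supportive and tested at 5%. The size of any gain rests on a correlation that the documents do not give, and every added baseline covariate brings missing values.

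All of this limits how much the point matters, and it stands. It does not explain the shorter list. The pain model also includes pre-operative opiate use, which is not a baseline value of pain, so the SAP does choose covariates for being prognostic and not only as own-baseline values.

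Three stronger readings are tempting and are not supported.
- **That omission pulls the odds ratio towards 1.** This is true of ordinary single-day logistic regression. The planned model has a participant random intercept, which largely absorbs an omitted participant-level covariate, and the simulation shows no material attenuation.
- **That the baseline Oxford Knee Score is wrongly omitted as well.** It is collected at baseline and covers pain and function. However, nothing in the documents ties it to fitness on days 0 to 3, and the SAP does not use it as a covariate for any early outcome.
- **That the planned analysis is biased or ignores the design.** The arms are randomised, and both stratification factors are in the model.

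**Conclusion.** The point holds as a minor, optional improvement. The fixed-effect list for fitness for discharge is inconsistent with the SAP's own pain models in leaving out baseline pain, and no reason is given.

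The size depends on an assumed correlation. In a model of the planned type, the standard error of the day-specific log odds ratio would fall by under 1% at 0.1, about 1% at 0.2, about 3% at 0.3 and 4% to 5% at 0.4. Over that range this is worth from under 1% to about 12% more patients, and about 1% to 14% in the simpler single-day check. A correlation of 0.4 already means an odds ratio of 2.94 per SD of baseline pain in this simulation, so the upper end needs a strong predictor. If baseline pain is not prognostic, essentially nothing is gained or lost.

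These figures rest on the assumed participant SD of 2.0, the assumed fitness rates and the terms left out of the simulation. The planned analysis remains valid, and the co-primary conclusions and the sample size are untouched.

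**What to change.** In SAP 6.2 (Secondary outcomes), before the final data lock, extend the fixed effects of the fitness-for-discharge model to *type of knee replacement, age, gender and baseline pain VAS*. Pre-operative opiate use could be added to match the pain model. If the shorter list is kept on purpose, one sentence giving the reason would be enough.

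The complications model in the same section takes its adjustment by reference to what comes before it, so state whether the extra covariate applies there too.

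Cost: one phrase, one or two more parameters and no new data. Missing baseline values should be handled as in the primary pain model, which needs the same variable. SAP 6.3 covers missing outcomes and questionnaire items but gives no rule for a missing baseline covariate, so one stated rule could serve both models.

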### 6.3 Missing Data

For each of the co-primary and secondary outcomes, the number and percentages of individuals in the missing category will be presented by treatment group, as well as reasons for missingness if known. The pattern of missingness will also be explored.

Based on the available data, the possibility of informative missingness, or data being missing not at random cannot be ruled out. Therefore, sensitivity analysis for missing data will examine the effect on the trial conclusions assuming that data are missing not at random, that is that those with missing data may have different outcomes than those with observed follow-up data.

Specifically, the potential effect of informatively missing data on the QoR-40 will be assessed using Stata's *rctmiss* command. Hereby outcomes for all of those with missing outcome data, and separately for those with missing outcome data in the treatment group, will be assumed to be, on average, up to 5 points worse than under a missing at random assumption. 5 points on the QoR-40 were chosen as this was the target difference used in the sample size calculation.

For the cumulative pain AUC analysis, the summary measures approach will be repeated based on the following imputations:

- Missing data at 6, 24, 48 and 72 hours for those in the whole sample known to have been discharged from hospital at the relevant timepoint will be replaced by a pain score of 3, i.e. the cut-off for participants being deemed fit for discharge.
- Missing pain scores at 6, 24, 48 and 72 hours for those in the whole sample not known to have been discharged from hospital by the relevant time point will be imputed with the worst pain score observed across both trial groups at this time point.

The main purpose of the sensitivity analysis for missing data is to examine if the change in the assumptions made about missing data change the trial conclusions.

For individual missing items on a questionnaire, the imputation rules will be as follows:

- QoR-40: if 3 or fewer answers are missing median imputation based on the other questions in the same domain will be used. If more than 3 answers are missing, the total score will be treated as missing.
- OKS: mean imputation based on the response to all other questions will be used for missing items on the OKS if 2 or fewer answers are missing. If more than 2 answers are missing, the total score will be treated as missing.
- AKSS: mean imputation will be applied to missing items in the patient satisfaction and expectations domains. If fewer than 50% of answers are missing, mean imputation based on the response to all other questions in the same domain will be used. If 50% or more of the answers are missing, the total score will be treated as missing. The functional score domain composes of four subgroups, including: walking and standing, standard activities, advanced activities and discretionary activities. No imputation will be undertaken for the walking and standing domain. Mean imputation will be used for standard and advanced activities domains. In the discretionary activities domain where participants are asked to select up to 3 activities and rate how much bother their knee gives them during this activity, if a patient indicates less than three activities, two assumptions will be investigated: (i) assume that where a discretionary activity is missing this doesn't necessarily mean they couldn't do any, therefore mean imputation will be used. If no activities are given, the discretionary activities score will be treated as missing. (ii) assume that where a discretionary activity is missing this is because the participant couldn't do any further discretionary activities, and a score of zero will be given for this activity (worst score). If no activities are given, the discretionary activities score will be treated as zero.

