#### 3.3 Sample Size

The trial has been powered for two primary endpoints, QoR-40 at 72 hours and cumulative pain score from 6-72 hours, with adjustment for multiplicity using the Bonferroni method [16]. The trial will be assessed as providing evidence of a difference if either of the two primary endpoints is statistically and clinically significant.

The study requires 240 patients per treatment arm in order to be 90% powered to detect a 5 point difference in global QoR-40 score between groups at a significance level of 0.025 (2-sided, adjusted for multiplicity) assuming the standard deviation is 15.5 [17]. To allow for 4% loss to follow-up this has been inflated to 500 patients (250 per treatment arm).

The study also requires a minimum of 225 patients per treatment arm in order to be 90% powered to detect a standardised difference of 33% between groups in cumulative pain score calculated as area under the curve from 6 to 72 hours post-surgery at a significance level of 0.025 (2-sided, adjusted for multiplicity). Inflating the sample size to 500 patients (250 per treatment arm) will allow for 10% loss to follow up on this variable.

Therefore a total of 500 patients will be randomised (250 per treatment arm).

Checks of the sample size calculations are detailed in the documents PAIN\_SS\_mar2016.rtf and QoR40\_SS\_mar2016 both stored in the confidential statistical section of the TMF.

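### At the planned 4% loss, the 5-point QoR-40 missing-not-at-random offset moves the estimate by at most 0.2 points; a two-directional tipping-point analysis would serve the SAP's purpose better

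*Combined protocol and SAP*

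**What the plan says.** SAP 6.3 accepts that missingness may be informative and sets the aim of the sensitivity analysis, which is to "examine if the change in the assumptions made about missing data change the trial conclusions".

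For QoR-40 it names Stata's rctmiss command and two scenarios: "Hereby outcomes for all of those with missing outcome data, and separately for those with missing outcome data in the treatment group" are taken to be, on average, "up to 5 points worse than under a missing at random assumption". The limit is justified in one sentence: "5 points on the QoR-40 were chosen as this was the target difference used in the sample size calculation".

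SAP 3.3 supplies the design values: "The study requires 240 patients per treatment arm in order to be 90% powered to detect a 5 point difference in global QoR-40 score", "at a significance level of 0.025 (2-sided, adjusted for multiplicity) assuming the standard deviation is 15.5". It allows 4% loss for QoR-40, which takes 240 to 250 per arm. A separate 10% allowance belongs to the pain AUC: "Inflating the sample size to 500 patients (250 per treatment arm) will allow for 10% loss to follow up on this variable". SAP 4.1 tests each co-primary at 2.5% with a 97.5% interval, and success on either makes the trial positive.

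For QoR-40 the SAP specifies no larger offset, no tipping-point search, no control-only scenario and no better-than-MAR scenario.

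**The concern.** The reason given for the 5-point limit mixes two quantities. The target difference is a contrast between arm means over all patients. The offset describes how far patients without a 72-hour score differ from what the model predicts for them. Nothing in the SAP argues that the first bounds the second. Five points is about 0.32 of the assumed SD (5/15.5), on a scale that runs from 40 to 200.

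Because the offset is diluted by the fraction missing, a limit that looks like a full target-sized effect becomes a small perturbation when few patients are missing. A finding that the conclusion did not change would then say little about how strong an informative mechanism the result could withstand.

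Direction matters too. Worsening only the intervention arm can only lower the estimated benefit. A result just short of significance is never tested against missing control patients doing worse, or missing intervention patients doing better, than predicted. The second is not far-fetched. Protocol 6.3 moves QoR-40 collection to daily telephone calls for patients discharged before 72 hours, and some who go home early and are not reached may be recovering well. That is a possibility, not something the documents establish.

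The SAP treats the other co-primary differently. In the same section, missing pain scores are set to the discharge cut-off of 3 for discharged patients and to the worst observed score for those not known to be discharged. QoR-40 gets neither a link to discharge nor an extreme scenario.

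**Working it through.** **Inputs.** Target 5 points, SD 15.5, two-sided alpha 0.025, power 90%, 240 per arm, 250 randomised per arm, 4% loss (SAP 3.3); 97.5% interval (SAP 4.1); offset 0 to 5 points worse (SAP 6.3). Missing fractions other than 4% are illustrative.

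**The plan's sample size reproduces.** n per arm = 2 × (2.2414 + 1.2816)² × (15.5/5)² ≈ 238.5, so 239 by the normal approximation. The noncentral-t calculation gives 240, as stated. 240/0.96 = 250.

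**Precision at 4% loss.** SE = 15.5 × √(2/240) = 1.415. Half-width = 2.2414 × 1.415 = 3.17 points.

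**Effect of the offset.** Let f_T and f_C be the fractions missing in the intervention and control arms, and d_T and d_C the offsets (negative for worse). Then

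shift in the estimate = d_T × f_T − d_C × f_C.

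- Intervention only, 5 points worse: the estimate falls by 5 × f_T. At 4% this is 0.20 points, or 0.20/1.415 = 0.14 SE.
- All missing, 5 points worse: the estimate falls by 5 × (f_T − f_C). This is zero if losses are equal. With 2% missing in control and 6% in intervention it is 5 × 0.04 = 0.20.

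**Which results could change.** A significant benefit is lost under the intervention-only scenario if the estimate lies between the half-width and the half-width plus 5 × f_T. The tipping offset is (estimate − half-width)/f_T. SE uses 250 × (1 − f) observed per arm.

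| Missing per arm | SE | Half-width | Largest shift | Estimates that could lose significance | Probability of that band if true difference is 5 | Tipping offset, estimate 5 | Tipping offset, estimate 4 |
|---|---|---|---|---|---|---|---|
| 4% (planned) | 1.415 | 3.17 | 0.20 | 3.17 to 3.37 | 2.7% | 45.7 | 20.7 |
| 10% | 1.461 | 3.28 | 0.50 | 3.28 to 3.78 | 8.2% | 17.2 | 7.2 |
| 20% | 1.550 | 3.47 | 1.00 | 3.47 to 4.47 | 20.5% | 7.6 | 2.6 |

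For an estimate equal to the 5-point target, the 5-point limit reaches the tipping point only when about 27% of the intervention arm is missing: at f = 0.27 the half-width is about 3.64, and 5 − 5 × 0.27 = 3.65.

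**The untested direction.** Take an estimate of 3.0 with 20% missing in each arm, which is not significant because 3.0 is below 3.47. It would become significant if missing intervention patients were (3.47 − 3.0)/0.20 ≈ 2.4 points better than predicted, or missing control patients 2.4 points worse. That offset is smaller than the SAP's own 5 points, yet neither planned scenario would show it. Intervention-only worsening takes 3.0 down to 2.0, and the all-missing scenario leaves it at 3.0.

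**The case against.** The strongest reply is that the small shift mostly reflects low planned missingness, which is good news and not a defect. With 4% missing and an estimate of 5, the tipping offset is about 46 points, roughly 3 SD. A tipping-point analysis would also conclude that the result is robust, and rightly. This stands. It also shows the benefit of reporting the tipping value: 46 points is evidence of robustness that a reader can judge, while surviving a 0.2-point shift is not.

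The planned intervention-only scenario is also the conservative direction for a superiority claim. With similar losses, a control-only better-than-MAR scenario would move the estimate the same way by about the same amount. This stands for a positive result, so the gap in direction matters mainly for a null one.

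Other provisions deal with missing data. Protocol 6.3 requires telephone follow-up with an additional call. Protocol 11.4 allows multiple imputation with sensitivity analyses. SAP 3.6 plans a blinded review of missingness, SAP 5.2 an investigation of differential losses, and SAP 6.2 a repeated-measures model. All reduce or describe the problem, but none supplies a wider MNAR range for QoR-40.

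A reader might infer that 0.2 to 0.5 points is a ceiling built into the plan. It is not. It is conditional on 4% to 10% missing, the 10% is the pain AUC allowance, and the shift grows in proportion to actual missingness, which the documents cannot give. Nor is the all-missing shift necessarily near zero; that requires balanced losses, which the documents do not state.

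**Conclusion.** The point holds in a limited form. The 5-point limit rests on a quantity that does not bound how non-responders might differ. At the planned 4% loss it moves the QoR-40 estimate by at most 0.2 points, against a half-width of about 3.2, so it can alter the conclusion only for an estimate of about 3.17 to 3.37. A null result is barely tested.

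It would be tempting to go further and say that the analysis cannot test robustness, or will report a robust result whatever the mechanism. The documents do not support that: a near-threshold result can change, and the analysis gains force as missingness rises (a 1.0-point shift and a 20.5% chance of falling in the affected band at 20% missing, if the true difference is 5).

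The figures assume SD 15.5, equal missing fractions when computing the SE, an SE held fixed as the offset varies, and no covariate adjustment. Adjustment for baseline QoR-40, age, gender, surgery type and centre would probably narrow the interval and move the band down, without changing the 0.2-point shift. The primary analysis is unaffected. This is a cheap improvement to a supporting analysis, not the correction of an error.

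**What to change.** In SAP 6.3, keep rctmiss but replace the 5-point limit with a tipping-point analysis:

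- Vary the offset in both directions, better and worse than MAR, until the 2.5%-level conclusion changes or the QoR-40 scale limit (40 or 200) is reached.
- Run it for the intervention arm only, the control arm only and both arms together.
- Report the tipping offset for each scenario beside the observed missing fraction in each arm, with a judgement on whether an offset of that size is plausible.

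The planned 5-point scenarios can stay as marked points on the same plot. The wording should be settled before the final data lock. The cost is a short SAP revision, one extra table or plot, and the need to make and defend a plausibility judgement. No new data are needed.
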